**Fig. 2 Fig2:**
[figure not shown]
Strategy for DNA library preparation and sequencing

### Sequencing data analysis

Custom adaptor sequences and low-quality bases will be removed by trimmomatic (v0.32). BWA-meth (0.2.2) will be used to align paired-end reads to CtoT and GtoA transformed hg19 genome respectively. After alignment, PCR duplicates will be marked by samblaster (v0.1.20), and reads with low mapping quality (MAPQ< 20) or paired improperly will be removed by sambamba (0.4.7) from further downstream analyses. Merge of paired reads sequence will be performed using in-house scripts, in which overlapping reads will be clipped to avoid double-counting of methylation calls.

### Sample size calculation

According to previous studies, the sensitivity of ctDNA methylation detection is above 70% in stage I lung adenocarcinoma [21]. So we assume our panel has a sensitivity of at least 70% in stage IA to III surgical patients. As our study focuses on early stage patients, we hypothesize the postoperative positive rate to be 15% during the 3-year follow-up, and assume a 85% follow-up rate. In the field of breast cancer and colon cancer, the recurrence rate within one year was over 50% in ctDNA-positive patients and less than 10% in ctDNA-negative patients [5, 7]. We assume ctDNA have similar prognostic prediction value in NSCLC patients. Given the information above, we plan to recruit 200 individuals for the final analysis. As a result, when alpha = 0.05, the two groups (postoperative positive vs. postoperative negative) would demonstrate statistical difference on DFS, with a power over 90%.

### Data analysis plan

Clinical pathological features and other information of recruited patients will be updated every day, and will be re-checked weekly by two thoracic surgeons. All the patients who meet the requirement of follow-up and sample collection will be included into the statistical analysis. Specific reasons will be recorded for patients who are excluded.

For statistics analysis, continuous variables will be expressed as a mean ± SEM (Standard Error of Mean), while categorical variables will be coded as analyzable forms. Kaplan–Meier method will be used to estimate the distributions of disease-free survival (DFS), and the log-rank test will be used to compare the distribution of survival time. Univariate and multivariate prognostic analyses will be performed using the Cox proportional hazard model. *P* values < 0.05 will be considered statistically significant. Analysis will be performed in the R statistical environment.

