Circulating tumor DNA (ctDNA) is a kind of tumor-specific DNA derived from tumor cells, which in principle contains the same genetic information of tumor tissue [4]. Detection of ctDNA with peripheral blood samples has been reported in different tumor types, especially in patients with advanced stage [5–7]. The eliminating rate of ctDNA is relatively high, making it an ideal biomarker to reflect tumor burden and providing a potential method for tumor management [4, 8–10]. In the field of non-small cell lung cancer (NSCLC), ctDNA has already shown its significance and gradually been recognized as a way to guide clinical practice [11–13]. However, previous researches focused mainly on patients of advanced stage (stage IIIB to IV). Studies of surgical patients (stage IA to III) were relatively rare, and data from early stage patients (stage IA to IIB) was especially scarce [14–16]. In addition, the amount of ctDNA is extremely low in early stage patients, increasing the difficulty of detection by sequencing, especially when there is a large amount of background cell free DNA (cfDNA) [4]. Although some institutions have explored the possibility of MRD detection after surgery, the sensitivity of ctDNA in early stage patients is not satisfying [17, 18]. In the recently published TRACERx study, the positive rate of ctDNA detected in stage I lung adenocarcinoma was only 19% [17]. To overcome these limitations, exploring multi-omics data may provide a promising strategy, such as integrating genetic and epigenetic information of ctDNA.

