### Previous work

The detection of ctDNA in late stage lung cancer has been well illustrated by previous studies. To evaluate the feasibility of ctDNA detection in surgical NSCLC patients, we enrolled 76 NSCLC patients who underwent curative-intent lung resection and analyzed their blood samples as well as tumor tissues using a 50 cancer related mutation panel. The overall concordance rate between plasma samples and tissue samples was 68.4%, and would increase according to TNM stage (stage I, 57.9%; stage II, 66.7%; stage IIIA, 90%, *P* = .043). Additionally, ctDNA was more sensitive compared with traditional tumor markers, and has higher predictive value than classic prediction models.^11 12^

Furthermore, we explored the stability and dynamic changes of ctDNA in surgical lung cancer patients. Plasma samples were obtained before (1 to 3 days) and during surgery for 20 patients. All ctDNA samples obtained before and during surgery had consistent mutations, and the mutation frequency varied at a very low level, indicating that plasma ctDNA offers reliable and consistent information. As dynamic changes of ctDNA in lung cancer patients remained to be clarified, we explored its half-life period and confirmed a rapid clearance after surgery. Three days after surgery was considered as an optimal start time for recurrence monitoring, as ctDNA concentration would reduce to zero theoretically. Interestingly, during the follow-up of postoperative patients, we found that ctDNA detection was in conformity with patients’ outcome [11, 12, 22].

To sum up, we have completed a series of studies in the field of liquid biopsy, demonstrated the feasibility of ctDNA detection in surgical NSCLC patients, and shown its potential value for postoperative surveillance.

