### Primary aims

To investigate the relationship between surgical lung cancer patients’ prognosis and quantitative changes in ctDNA mutations and aberrant methylation.To investigate the variation of aberrant methylated ctDNA concentration before surgery, 3 days after surgery and 1 month after surgery.

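### Mean ± SEM, the only summary stated for continuous variables, suits the ctDNA concentrations of the second primary aim poorly, above all after surgery when most values are expected at or near zero

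*Protocol article*

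**What the plan says.** The Data analysis plan sets one rule for describing continuous data: "continuous variables will be expressed as a mean ± SEM (Standard Error of Mean". No other summary is named and no variable is exempted. The other methods in that section (Kaplan–Meier, log-rank, Cox) concern disease-free survival and prognosis.

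The second item under Primary aims is a continuous measure at three time points: "To investigate the variation of aberrant methylated ctDNA concentration before surgery, 3 days after surgery and 1 month after surgery".

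Three other statements indicate what those values will look like:

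- Previous work gives the reason for starting monitoring three days after surgery: "as ctDNA concentration would reduce to zero theoretically".
- Background says that "the amount of ctDNA is extremely low in early stage patients".
- Sample size calculation states: "we hypothesize the postoperative positive rate to be 15% during the 3-year follow-up, and assume a 85% follow-up rate". For detection in general it states: "So we assume our panel has a sensitivity of at least 70% in stage IA to III surgical patients".

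The planned size is given as "we plan to recruit 200 individuals for the final analysis". Under Sample collection, patients lacking any of blood samples A (before surgery), B (day 3) or C (one month) are excluded from analysis.

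**The concern.** A mean with its SEM says how precisely an average has been estimated. It does not say how much patients differ or what a typical patient's value is. For roughly symmetric variables that is a minor fault, cured by giving the SD.

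For postoperative ctDNA it is more than that. The study rests on a split between a majority who clear ctDNA and a minority who do not. If most values at samples B and C are at or near zero, the mean is set by the minority. The reader could not tell from mean ± SEM how many patients cleared, or whether a fall in the mean reflects most patients or a few with high starting values.

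At stake is the description of the perioperative concentration aim, which is due to be reported first at the interim analysis of samples A to C.

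**Working it through.** **The plan's own figure.** The article gives no computed figure for this aim. Its one computed design figure is power over 90% for DFS, and it reproduces. Take one-year recurrence of 50% against 10%, a 15:85 split and two-sided alpha 0.05 (sidedness is not stated).

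- Two proportions: 99.7% at N = 200 and 99.2% at N = 170.
- Schoenfeld, with HR = ln 0.5 / ln 0.9 = 6.58: events at N = 200 are 30 × 0.5 + 170 × 0.1 = 32, giving 96.7%. With 27.2 events at N = 170 it is 93.9%.

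None of this uses mean ± SEM.

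**Inputs for the present point**

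- n = 200 (Sample size calculation), or 200 × 0.85 = 170 if only those followed are counted.
- Share positive after surgery: 15% over three years. If this means ever positive in that period, the share positive at day 3 or month 1 alone is no higher.
- Share detectable before surgery: at least 70%.
- Assumed, not in the article: negatives are exactly zero, and positives are either all equal or log-normal with log-SD s of 1.0 or 1.5.

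**Step 1: SEM against SD (no distributional assumption).** SEM = SD/√n.

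- n = 200: 1/14.14 = 7.1% of the SD.
- n = 170: 1/13.04 = 7.7% of the SD.

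**Step 2: what the mean shows at samples B and C.** At 15% positive, 0.15 × 200 = 30 patients carry the entire mean and the other 170 contribute nothing. The median and both quartiles are 0. The mean equals the positive share times the average level among positives, so different clearance patterns can give the same mean:

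- 30 of 200 positive at level 1: mean 0.15, SD = √(0.15 × 0.85) = 0.357, SEM 0.025.
- 15 of 200 positive at level 2: mean 0.075 × 2 = 0.15, SD = √(0.075 × 4 − 0.15²) = 0.527, SEM 0.037.

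Clearance is 85% in one case and 92.5% in the other. The reports would read 0.15 ± 0.025 and 0.15 ± 0.037.

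**Step 3: spread and skewness.** With positive share p and log-SD s, (SD/mean)² = exp(s²)/p − 1.

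| p | Positives equal (s = 0) | s = 1.0 | s = 1.5 |
|---|---|---|---|
| 0.15 | 2.4 | 4.1 | 7.9 |
| 0.30 | 1.5 | 2.8 | 5.5 |

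The entries are SD/mean. At p = 0.15, the share of patients below the mean is 85% if positives are equal, 86.2% at s = 1.0 and 89.5% at s = 1.5. At p = 0.30 the median is still 0, so the conclusion does not hinge on the 15%.

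**Step 4: sample A.** At p = 0.70 the median is not zero. With log-normal positives, the mean is 0.70 × exp(s²/2) and the median solves 0.30 + 0.70 × Φ(ln m / s) = 0.5.

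- s = 1.0: mean 1.15, median 0.57.
- s = 1.5: mean 2.16, median 0.43.

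Skewness of this size would still separate mean from median, but it rests on the assumed tail. The argument from values at zero does not apply here.

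**The case against.** The other side has a good deal to say.

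- **The SEM is a legitimate, labelled quantity.** It gives the precision of a mean, and the SD can be recovered as SEM × √n. This stands. The fault is its use as the only descriptive summary. Recovering the SD would not give the percentage cleared, nor describe a skewed distribution.
- **The aim's wording.** A reader might take the word variation to mean spread between patients and see a direct clash with the SEM. The aim lists three time points, so the natural meaning is change over time. No such clash is supported.
- **Pairing.** A reader might infer that means at A, B and C will be compared as if they came from different patients. The article states no test for that comparison, paired or unpaired, and requires all three samples from every analysed patient, so paired data will exist. Silence on the test is not a finding.
- **Striking ratios.** One could stress that the SEM is about 14 times smaller than the SD, or that very few patients lie within mean ± SEM. The first is simply √200 and holds for any variable. The second is uninformative: even for a normal variable at n = 200 the share is 2Φ(0.0707) − 1, about 5.6%. Neither is evidence about ctDNA.
- **Zeros are partly inferred.** The expected fall to zero comes from the team's earlier ctDNA work, which the article describes with a mutation panel. A negative call means below a threshold. Methylation signal may have background, and no detection limit is given. This stands: the supportable wording is at or near zero in most patients.
- **Other ctDNA results are planned.** Positive and negative groups are compared on DFS, and sensitivity, specificity and stability are to be reported. So ctDNA will not be characterised by mean ± SEM alone, although that remains the only stated summary of concentration.

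**Conclusion.** The point holds in a limited form. The article fixes a single summary for all continuous variables, and that summary suits the concentration data of its second primary aim poorly. This is a stated choice, not a detail left to a fuller document.

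That the SEM is about 7–8% of the SD at 170–200 patients, and so does not display spread, needs no assumption. That the mean at samples B and C would be driven by a small group and hide the proportion cleared rests on the article's own expectations: clearance by day 3, very low amounts, and 15% positive. It also assumes that this 15% covers the early samples and that negatives sit close to zero. The numerical illustrations rest further on the assumed tail. At sample A only the SEM point and likely skewness apply.

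The effect is confined to describing and interpreting the concentration aim. A reader might infer that the prognostic results or the sample size are undermined. They are not: the log-rank test, the Cox models and the stated power do not use this summary. The change is worth making because it is cheap and concerns a primary aim, but it is not a design flaw.

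**What to change.** In the Data analysis plan, replace the single mean ± SEM rule with the following:

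- For ctDNA measures at A, B and C, report the median and IQR, and the percentage detectable with a 95% CI.
- Describe the change from A to B and from A to C within patients, by a rank-based or log-scale method that allows for undetectable values.
- For roughly symmetric variables such as age, report mean ± SD.

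This needs no new patients, samples or visits, and no change to the DFS analyses or the sample size. The cost is slightly more analysis work, chiefly in handling undetectable values in the change from baseline.

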### Duration of study

We designed a two-step plan for this study. We started recruitment from August 2018, and expected to successfully recruit 200 patients by August 2019. By December 2019, we plan to have generated data on all the baseline and first follow-up samples, including tissue samples (Sample T, Sample N2, and Sample N5) and blood samples (Blood Sample A to C) for ctDNA mutation and methylation detection. Meanwhile, we plan to carry out an interim analysis, including analyzing the data of ctDNA detection integrated with the corresponding clinical pathological features, comparing and associating characteristics of ctDNA methylation and mutation data among this whole cohort of early stage NSCLC patients, including but not limited to sensitivity, specificity and stability.

In the final analysis, which we expect to carry out in August 2022 with the complete follow-up data collected, the feasibility and clinical utility of ctDNA mutation and methylation detection as a means of lung cancer surveillance will be fully analyzed. As the conclusion of the study, we plan to propose a practical strategy for postoperative management of NSCLC.

This program will finish after all the patients have a 3-year follow-up.

## Discussion

Previous studies have shown that detection of ctDNA in the blood of postoperative patients is closely related to unfavorable prognosis in different tumor types, regardless of TNM staging and clinical pathological features. Postoperative patients with positive ctDNA were reported to have significantly higher recurrence rate, indicating that ctDNA may provide vital information of minimal residual disease [5, 7]. However, the detection of ctDNA in early stage lung cancer, especially adenocarcinoma, is relatively low [17]. This becomes one of the bottlenecks for the application of ctDNA currently.

On the other hand, DNA derived from tumor cells contains epigenetic information that can be detected in blood samples. Several studies have focused on the methylation of tumor tissue DNA and shown it can be used as a method of diagnosis and prognostic prediction. Aberrant DNA methylation can be detected in histological negative lymph node, and is related to poor prognosis, indicating some minimal residue disease (MRD) can be detected by this method [20]. However, detection of methylations of ctDNA has not been well established for clinical application yet. Most previous studies focused on aberrant methylations in tumor tissues, and used different panels of promoter sites. Some studies tested serum samples rather than plasma samples, indicating there still exists inconformity of specimen processing [6, 21]. Moreover, most of the previous researches were retrospective studies, which may cause insufficient assessment of the prognosis outcome and restricts the application of this method. For surgical lung cancer patients, the rationality, practicability, and stability for detection of aberrant ctDNA methylations are not illuminated systematically. And the optimal panel for NSCLC patients is still unclear.

This is the first registered study designed to prospectively evaluate and compare the detection of aberrant methylation and mutations in ctDNA among stage IA to III surgical NSCLC patients for the surveillance. The fundamental purpose of this study is to investigate the feasibility of ctDNA methylation and mutations detection as a means of lung cancer surveillance. Additionally, by analyzing the plasma samples before and after surgery, we can compare and associate biological characteristics of ctDNA methylation and ctDNA mutations. With the 3-year follow-up data, we will be able to compare the sensitivity, specificity, stability and clinical utility of the two methods, and thus propose a multi-omics information based follow-up strategy.

We expect this study can define an effective strategy for postoperative surveillance of lung cancer, by integrating liquid biopsy with current clinical practice. This may renew our knowledge of the high risk postoperative populations, and may provide new indications of adjuvant therapy [23]. However, large-scale prognostic clinical trials will be required before liquid biopsy based adjuvant therapy coming into clinical practice. In addition, this is a single institutional clinical study with a relatively long follow-up period. As a result, selection bias as well as follow-up bias may exist. Future investigations may provide complementary information of different populations.

## Data Availability

Unpublished data will be available from the corresponding author on reasonable request.

## Abbreviations

CA-125: Carbohydrate antigen 125
CA-199: Carbohydrate antigen 199
CEA: Carcinoembryonic antigen
cfDNA: Cell free DNA
CT: Computed Tomography
ctDNA: Circulating tumor DNA
CYFRA21-1: Cytokeratin 19 fragment
DFS: Disease-free survival
IL-6: Interleukin 6
MRD: Minimal residual disease
MRI: Magnetic Resonance Imaging
NSCLC: Non-small cell lung cancer
NSE: Neuron-specific enolase
PET: Positron Emission Tomography
pGGO: Pure ground glass opacity
SEM: Standard Error of Mean
